### Determination of endpoints

#### Spirometric assessment of lung function

Lung function will be assessed by spirometry according to pneumological routine protocols. FEV_1_ and FVC will be recorded amongst other routine spirometric parameters and interpreted according to the latest edition of joint European Respiratory Society / American Thoracic Society Guideline on spirometry [24, 25] as the best values reached by a patient during three repeated spirometry runs on each clinical investigation to assess pulmonary function. FEV_1_ results will be analyzed against age- and sex-controlled normal ranges (LLN = lower limit of the normal range) [26], and their change between baseline investigation and the last investigation during follow-up of this study will be calculated to assess the percent change in FEV_1_ (percent of LLN), which is the primary end-point of the study.

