**Methods:**

148 COPD patients (GOLD stage 2–3, groups B or C) will undergo exercise testing with continuous pulse oximetry. They will be followed for 36 months by spirometry, echocardiography, endothelial function testing, and biomarker analyses. Exercise testing will be performed by comparing the 6-min walk test (6MWT), bicycle ergometry, and a 15-sec breath-hold test. Exertional desaturation will be defined as SpO_2_ < 90% or delta-SpO_2_ ≥ 4% during the 6MWT. The primary endpoint will be the rate of decline of FEV1(LLN) between COPD patients with and without exertional desaturation.

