## Methods

### Study design

PROSA is a monocenter, observational, prospective cohort study. 148 patients with chronic obstructive lung disease (COPD) stages 2–3, groups B and E according to GOLD [7] will be enrolled in this clinical study. We expect that one third of our study cohort will experience exertional hypoxemia based on incidence rates reported in previous studies [22, 23]. Patients will be recalled to the study site once per year for a total of 36 months of follow-up.

The primary endpoint of the study will be the difference in FEV_1_ (LLN) over time in COPD patients with exertional desaturation versus those without exertional desaturation (exertional desaturation will be defined as oxyhemoglobin saturation by pulse oximetry (SpO_2_) < 90% or a drop of SpO_2_ ≥ 4% during a six-minute walk test [19].

Secondary endpoints have been defined as follows: (1) The difference in all-cause mortality over time in COPD patients with exertional desaturation versus those without exertional desaturation. (2) The difference in COPD-related mortality over time in COPD patients with exertional desaturation versus those without exertional desaturation. (3) The difference in frequency of hospital admissions for exacerbation of COPD in COPD patients with exertional desaturation versus those without exertional desaturation. (4) The difference in frequency of hospital admissions for causes other than exacerbation of COPD in COPD patients with exertional desaturation versus those without exertional desaturation. (5) The sensitivity and specificity of plasma biomarkers at baseline to predict the prevalence of exertional desaturation in COPD patients. (6) The sensitivity and specificity of plasma biomarkers at baseline to prospectively predict the slope of lung function decline in COPD patients. (7) The sensitivity and specificity of plasma biomarkers at baseline to prospectively predict the mortality rate in COPD patients. (8) The difference in incidence and extent of exercise hypoxemia between carriers and non-carriers of single nucleotide polymorphisms in genes of the L-arginine – dimethylarginine pathway. (9) The difference in positive and negative predictive value of bicycle ergometry, 6-minute walk test, and 15-sec breath-hold test to discriminate between COPD patients with exertional desaturation versus those without exertional desaturation.

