### Statistical analysis

Statistical analyses will be performed using the SPSS Version 27 software package (IBM Corporation, Armonk, NY, USA) and GraphPad Prism (version 6.01, GraphPad Software, San Diego, CA, USA) in the investigational center. All variables will be tested for normal distribution using the Kolmogorov–Smirnov test. Data will be expressed as mean with standard deviation (SD). Differences between groups will be tested for significance using the nonparametric Mann–Whitney U test for two groups or the Kruskal–Wallis analysis of variance for more than two groups. The Chi^2^ test will be used for comparison of categorical variables between groups. Logistic regression will be used to assess the relationship between exertional hypoxemia and mortality. The nil hypothesis for statistical evaluation of the primary endpoint will be that the difference in FEV_1_ (LLN) at 3 years of follow-up will not be different between COPD patients with exertional desaturation versus those without exertional desaturation. Exertional desaturation will be defined as oxyhemoglobin saturation by pulse oximetry (SpO_2_) < 90% or a drop of SpO_2_ ≥ 4% during a six-minute walk test [19].

Survival analyses will be performed using Kaplan–Meier curves comparing patients with or without exertional hypoxemia, and with ADMA and SDMA above or below the cut-off value determined in receiver-operated curve (ROC) analyses. Hazard ratios (HR) and 95% confidence intervals (CI) will be calculated by multivariable-adjusted logistic regression analyses. For all tests, *p* < 0.05 will be considered statistically significant. A correction of p will be performed for multiple comparisons when adequate.

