### Sample size discussion

Sample size estimation was based on analysis with repeated-measures 2-way ANOVA (baseline – 1 year – 2 years – 3 years). We assume that one third of our study cohort will experience exertional hypoxemia as reported in previous studies [22, 23], and we estimate that a 20% difference in the primary endpoint will be of clinical significance. To prove or dismiss the primary endpoint with α = 0.05 and a power of 0.90, a total sample size of 148 COPD patients stages 2–3, groups B and E according to the current GOLD guideline [7] will be included in this study after accounting for an expected drop-out rate of up to 15%.

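### The primary endpoint is defined in conflicting ways, and under one of them (unscaled change to the last visit) unequal drop-out could shrink the difference the study seeks

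*Protocol article*

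**What the plan says.** The protocol article describes the primary endpoint in five places.

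- **Abstract, Methods:** "The primary endpoint will be the rate of decline of FEV1(LLN) between COPD patients with and without exertional desaturation". This is scaled for time.
- **Study design:** "The primary endpoint of the study will be the difference in FEV_1_ (LLN) over time in COPD patients with exertional desaturation", compared with patients without it. No estimator is named.
- **Spirometric assessment of lung function:** for FEV1 against the lower limit of normal, "their change between baseline investigation and the last investigation during follow-up of this study will be calculated", in order "to assess the percent change in FEV_1_ (percent of LLN), which is the primary end-point of the study". This is the only place that says how the endpoint is computed, and nothing is divided by time.
- **Statistical analysis:** the null hypothesis is that "the difference in FEV_1_ (LLN) at 3 years of follow-up will not be different between COPD patients" with and without desaturation. For comparing two groups this section names the Mann–Whitney U test.
- **Sample size discussion:** "Sample size estimation was based on analysis with repeated-measures 2-way ANOVA", with baseline and three yearly visits as the time points.

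Three other statements bear on the point. Study conduct and funding schedules spirometry at 0, 12, 24 and 36 months and ends the study for each patient at month 36. The sample size allows for drop-out of up to 15%, not split by group. The Background cites an association of desaturation during the walk test with faster lung function decline and with high mortality.

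**The concern.** The five descriptions agree for a patient who attends every visit and differ for one who does not. A rate can use partial follow-up and scale it correctly. A 3-year comparison cannot use it without some rule for missing values. An unscaled change to the last visit uses it but treats it as if it were complete.

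This matters because the comparison is between two groups whose follow-up may differ in length. If desaturators die or withdraw earlier, an unscaled change records less of their decline, which works against the hypothesis under test. The Abstract presents the study as one that will settle that hypothesis either way. If the choice between versions stays open until the data are seen, the conclusion could depend on which one is picked.

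**Working it through.** **The plan's own figure.** The total of 148 cannot be rebuilt, because the article states no standard deviation and no within-patient correlation. The drop-out step is consistent: 125/0.85 = 147.1, rounded up to 148. At the 15% ceiling, 148 × 0.15 = 22.2, so the definitions could diverge for about 22 patients.

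**Inputs from the article.** Yearly visits to month 36; one third of the cohort desaturating (1:2); drop-out up to 15% overall; a 20% difference regarded as clinically significant.

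**Assumptions that are not in the article.** Decline is linear. The 20% means that desaturators decline 1.2 times as fast. Drop-outs are last seen at month 12 or month 24 equally often, so 1.5 years on average. Within a group, drop-outs decline at the same rate as completers. The splits of drop-out between groups are chosen so that each gives 15% overall.

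**Reading A: each patient's last attended visit.** With drop-out proportion q:

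- mean follow-up in years = 3(1 − q) + 1.5q = 3 − 1.5q
- observed ratio = 1.2 × (mean follow-up, desaturators) / (mean follow-up, others)
- share of the true 3-year difference kept = (1.2 × follow-up of desaturators − follow-up of others) / 0.6, where 0.6 = 3 × 0.2

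| Drop-out, desaturators / others | Overall | Mean follow-up (years) | Observed ratio | Share of difference kept |
|---|---|---|---|---|
| 15% / 15% | (15 + 2 × 15)/3 = 15% | 2.775 / 2.775 | 1.20 | 92.5% |
| 20% / 12.5% | (20 + 2 × 12.5)/3 = 15% | 2.700 / 2.8125 | 1.15 | 71% |
| 25% / 10% | (25 + 2 × 10)/3 = 15% | 2.625 / 2.850 | 1.105 | 50% |
| 30% / 7.5% | (30 + 2 × 7.5)/3 = 15% | 2.550 / 2.8875 | 1.06 | 29% |

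A 20% faster decline is cancelled completely when desaturators' mean follow-up is 1/1.2 = 83% of the others', for example 2.5 against 3.0 years.

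**Reading B: month 36 only.** Follow-up is 3 years for everyone analysed, so under the same assumptions the ratio stays at 1.20 in every row. Early leavers are lost. That costs information, and it biases the result only if they decline differently from completers in their group.

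**Illustrative power.** Simulation with 49 and 99 patients, mean slopes of −3.6 and −3 points per year, slope SD 0.8, residual SD 0.8, baseline SD 10, and drop-out unrelated to slope. None of these values is in the article; they give a setting in which a 20% difference is detectable.

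| Drop-out, desaturators / others | Change to last visit, Mann–Whitney | Month 36 completers, Mann–Whitney | Mixed-model slope |
|---|---|---|---|
| 15% / 15% | about 86% | 93% | 96–98% |
| 25% / 10% | about 40% | 92% | 96–98% |
| 30% / 7.5% | about 20% | 91% | 96–98% |

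The absolute levels depend on the assumed variances. The pattern does not: only the unscaled change to the last visit loses power steeply as drop-out becomes unequal.

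**The case against.** The strongest reply is that the last investigation simply means the month-36 visit. The article closes the study for each patient at that visit, sets its null hypothesis at 3 years, and enlarges the sample for drop-out, a step that fits best if drop-outs contribute nothing. For anyone seen at month 36, the change to the last visit, the 3-year change and the average annual rate are the same quantity up to a constant. This stands as a plausible reading, perhaps the better one. It does not settle the matter, because the computing rule does not name month 36, the Abstract speaks of a rate, and a four-visit ANOVA is not a two-group rank test of a single change.

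A reader might also infer three stronger things that the documents do not support:

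- **That desaturators will be followed for less time.** The cited association with mortality makes this plausible, but no deaths or drop-out are given by group, and 15% is an overall ceiling. Equal drop-out leaves the ratio at 1.20 and costs 7.5% of the absolute difference.
- **That the plan therefore does hide faster decline.** This needs both Reading A and unequal drop-out. The large losses in the table need desaturators to leave 2.5 to 4 times as often as the others.
- **That both readings bias against the hypothesis.** Under the assumptions above, the month-36 analysis keeps the ratio at 1.20. Survivor bias is possible, but neither its presence nor its direction follows from the article.

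The handling of missing data may be set out in a full protocol or analysis plan that is not shown. That answers a complaint about missing detail. It does not answer one about conflicting statements in the text itself.

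**Conclusion.** The point holds as a conflict in the definition of the primary endpoint. The five descriptions imply different estimands, different patients and different tests. One of them, the unscaled change to the last visit, can bias the comparison. With 15% overall drop-out under the assumptions stated, a true ratio of 1.20 would appear as anything from 1.20 (equal drop-out) to 1.06 (30% versus 7.5%). That range is conditional on reading the last investigation as each patient's last attended visit and on splits of drop-out that the article does not give. On the month-36 reading there is no artefact from length of follow-up. What remains is lost information, and a bias only if those who leave or die decline differently from those who stay. The conflict should be resolved before the data are analysed, whichever reading was intended.

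**What to change.** State one primary estimand in the Abstract, Study design, Spirometric assessment, Statistical analysis and Sample size discussion: the between-group difference in annual change of FEV1 (percent of LLN per year). Estimate it as the group-by-time term of a linear mixed model with random intercept and slope, using every spirometry at 0, 12, 24 and 36 months. Delete the unscaled change to the last investigation and the separate 3-year null hypothesis, and express the 20% difference in terms of the annual change.

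The cost is mainly wording. Yearly spirometry is already scheduled, SPSS (already named) fits such a model, recruitment is ongoing and results are expected in 2028. The sponsor should confirm that the stated 90% power carries over, since it was derived for a repeated-measures ANOVA.

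There is a small downside. The model assumes roughly linear decline and drop-out that is ignorable given the observed data, and patients lost before month 12 contribute only a baseline value. A sensitivity analysis for informative drop-out or death is advisable. A joint model of slope and death is one option, but it is not essential to this correction.

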#### Assessment of exertional hypoxemia

Three different approaches will be used to assess if patients experience intermittent hypoxemia. All of these clinical approaches have been used before in clinical investigations with COPD patients, but the diagnostic utility of these different procedures has not been assessed in direct comparison. First, patients will be asked to perform a 15-second breath-holding test under supervision by study personnel while arterial oxygen saturation is continuously recorded with a pulse oximetry device clipped to a fingertip [20]. After a few minutes of rest, patients will perform a 6-minute walk test according to the guidelines of the American Thoracic Society [27] under supervision by study personnel while arterial oxygen saturation is continuously recorded with a pulse oximetry device clipped to a fingertip. The walk test will be performed indoor, and the total distance walked during 6 min by the patient will be recorded together with the lowest arterial oxygen saturation during the test. After another resting period, patients will undergo bicycle ergometry according to a protocol published by Miki and colleagues [21]. Ergometry will be performed under supervision by an investigator while arterial oxygen saturation is continuously recorded with a pulse oximetry device clipped to a fingertip. The exercise protocol will consist of a steady-state resting period of at least 3 min, followed by workload increments of 5 W every minute starting at 0 W until patient exhaustion in the sitting position using a bicycle ergometer (Ergoselect 100P, Ergoline, Bitz, Germany). Arterial oxygen saturation will be continuously recorded with a pulse oximetry device clipped to a fingertip; blood pressure readings will be done every minute during the last 15-s period of each stage.

#### Determination of NO-mediated vasodilation in the brachial artery

Flow-mediated vasodilation in the brachial artery is a non-invasive measure of endothelial nitric oxide release that has been shown to be an early sign of systemic cardiovascular disease [28]. This investigation will be performed according to the guidelines published by the International Brachial Artery Reactivity Task Force [29]. The brachial artery will be imaged transcutaneously with a high-resolution ultrasound probe on the right forearm (Samsung HV70 EVO; Samsung, Schwalbach, Germany). The mean brachial artery diameter will be measured on a 2 cm longitudinal segment with Brachial Analyzer 6 software (Medical Imaging Applications LLC, Coralville, Iowa, USA). The difference in brachial artery diameter from baseline to hyperemia after 5 min of suprasystolic occlusion at the upper arm with a blood pressure cuff will be calculated to express endothelium-dependent, NO-mediated vasodilation (%). After ten minutes of rest, another baseline image will be recorded, followed by the administration of one sublingual spray burst of glyceryl trinitrate, and image acquisition at 60–90 s. later to assess endothelium-independent, NO-mediated vasodilation (%).

#### Echocardiographic assessment of the right ventricle and pulmonary arterial pressure

Echocardiography will be performed according to routine cardiological imaging procedures using a Samsung HM70 EVO echocardiography system with a PN1-5 phased-array probe (1–5 MHz). Imaging studies will include measurements of cardiac output, right ventricular pressure gradient, and estimations of right atrial pressure.

#### Biomarkers and genotyping

Blood samples from an antecubital vein and capillary blood will be collected for analysis of L-arginine-related biomarkers, genotyping of genes in L-arginine metabolic pathways, platelet aggregation, and routine clinical chemical and hematological parameters.

### Ethical conduct

The PROSA study will be conducted in agreement with the principles set forth in the Declaration of Helsinki in its latest revision adopted in Fortaleza, 2013. The study protocol has been submitted for review to the responsible Ethics Committee (Ethics Committee of the Hamburg Board of Physicians) and received a positive vote (2024-101240-BO-ff; dated 21.02.2024). The protocol has been registered with clinicaltrials.gov (register no. NCT06265623, dated 09.02.2024).

### Study conduct and funding

The PROSA study is exclusively being funded by the European Commission as part of the European Research Council Advanced Grant Project “NO PRESSURE” (Regulation of the L-Arginine – ADMA – Nitric Oxide (**NO**) Pathway in the **P**ulmonary Vascular **Res**ponse to Hypoxia and its Role for **Sur**vival of High-Risk COPD Pati**e**nts; Proposal NO. 101,096,706).

Patients who are selected by their primary physician or pulmonology specialist as suitable for participation in the study and who are willing to undergo screening for the study will be screened by the investigators according to the inclusion and exclusion criteria. Patients who fulfil the inclusion and exclusion criteria will be informed about the scope, aims, and possible risks of the study, and after having given their written informed consent, will undergo baseline investigation (study day 1).

Investigations on study day 1 will comprise peripheral venous blood sampling and capillary blood sampling, assessment of endothelial function by measuring flow-mediated vasodilation on the forearm by ultrasound, echocardiography, spirometry, and exercise testing. The total duration of these studies is estimated to take 2.5–3 h per patient.

After completing clinical investigations on study day 1, patients will be released into ongoing primary medical care. The second investigation (study day 2) will be scheduled at 12 months after the first study day, and additional studies will take place at 24 months (study day 3) and 36 months (study day 4) after the first study day. On each of these follow-up study days, patients will be asked about their health status during the preceding 12 months, with special focus, but not exclusively, on clinical symptoms and possible exacerbations of their COPD. Thereafter, the same clinical investigations as described for study day 1 will be repeated in identical manner. After the end of study day 4, i.e. at 36 months, the study will be completed for each patient.

### Statistical analysis

Statistical analyses will be performed using the SPSS Version 27 software package (IBM Corporation, Armonk, NY, USA) and GraphPad Prism (version 6.01, GraphPad Software, San Diego, CA, USA) in the investigational center. All variables will be tested for normal distribution using the Kolmogorov–Smirnov test. Data will be expressed as mean with standard deviation (SD). Differences between groups will be tested for significance using the nonparametric Mann–Whitney U test for two groups or the Kruskal–Wallis analysis of variance for more than two groups. The Chi^2^ test will be used for comparison of categorical variables between groups. Logistic regression will be used to assess the relationship between exertional hypoxemia and mortality. The nil hypothesis for statistical evaluation of the primary endpoint will be that the difference in FEV_1_ (LLN) at 3 years of follow-up will not be different between COPD patients with exertional desaturation versus those without exertional desaturation. Exertional desaturation will be defined as oxyhemoglobin saturation by pulse oximetry (SpO_2_) < 90% or a drop of SpO_2_ ≥ 4% during a six-minute walk test [19].

Survival analyses will be performed using Kaplan–Meier curves comparing patients with or without exertional hypoxemia, and with ADMA and SDMA above or below the cut-off value determined in receiver-operated curve (ROC) analyses. Hazard ratios (HR) and 95% confidence intervals (CI) will be calculated by multivariable-adjusted logistic regression analyses. For all tests, *p* < 0.05 will be considered statistically significant. A correction of p will be performed for multiple comparisons when adequate.

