The PROSA study (Prospective observational study to assess the influence of intermittent hypoxaemia on lung function decline, morbidity, and mortality in COPD patients) was designed to generate definite evidence for the association of exertional hypoxaemia with lung function decline and outcome in COPD patients. Beyond this, the study aims to elucidate pathophysiological mechanisms underlying this relationship and potential biomarkers that may help to better identify COPD patients at high risk of rapid disease progression at an early time point during their disease course.

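### The analysis section and the sample-size section do not name the same primary analysis, and the only listed test that fits compares non-randomised groups without adjustment

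*Protocol article*

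**What the plan says.** Three parts of the Methods bear on the primary comparison.

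- **Statistical analysis.** The rule for continuous outcomes is "Differences between groups will be tested for significance using the nonparametric Mann–Whitney U test for two groups", with Kruskal–Wallis for more than two groups and chi-squared for categorical data. The primary null hypothesis is a two-group contrast in FEV1 (LLN) at three years, with no covariate named. Multivariable adjustment appears once, for hazard ratios, which "will be calculated by multivariable-adjusted logistic regression analyses".
- **Sample size discussion.** "Sample size estimation was based on analysis with repeated-measures 2-way ANOVA", with baseline and years 1, 2 and 3 as the time points. The 148 patients, α = 0.05, power 0.90 and drop-out of up to 15% follow from it.
- **Spirometric assessment of lung function.** FEV1 results "will be analyzed against age- and sex-controlled normal ranges", and "their change between baseline investigation and the last investigation during follow-up of this study will be calculated" as the basis of the primary endpoint.

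The Study design section states that "PROSA is a monocenter, observational, prospective cohort study". The groups are formed by SpO2 during the six-minute walk test. The Background says the study "was designed to generate definite evidence for the association of exertional hypoxaemia with lung function decline and outcome in COPD patients".

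**The concern.** A power statement holds only for the analysis it was computed for. Here the study is sized on a four-visit ANOVA, while the analysis section offers a rank test for two groups. The two use different data and estimate different things.

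The rank test also fits the question poorly. Applied to change from baseline to the last visit, it ignores the 12- and 24-month spirometries of every patient who completes follow-up. It yields no adjusted slope difference with a confidence interval, although the abstract describes the endpoint as a rate of decline. It cannot take covariates either.

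That last point matters most in a cohort. Desaturators are not a random third of the patients. If they differ at baseline in anything that predicts decline, the unadjusted test attributes that difference to desaturation. An imbalance in the opposite direction would hide a real difference. At stake is whether a significant primary result could be read as evidence about desaturation itself, or as information beyond what baseline severity already gives.

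**Working it through.** **1. The plan's own figure.** The article gives no SD, reference decline or within-patient correlation, so 148 can be neither reproduced nor refuted. For a four-visit repeated-measures ANOVA at 90% power and α = 0.05, with assumed f of 0.1 to 0.25 and within-patient correlation of 0.5 to 0.9, totals after 15% drop-out run from 10 to 1,146, depending also on whether the interaction or the between-group effect is tested. The figure cannot be tied to one set of inputs.

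**2. Evaluable patients.** 148 × 0.85 = 125.8, about 126. With one third desaturating, as the Sample size discussion assumes, that is 42 against 84.

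**3. Does the rank test itself cost power?** For a single change score, two-sided α = 0.05 (sidedness is not stated) and 90% power, the detectable standardised difference is

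d = (1.960 + 1.282) × √(1/42 + 1/84) = 3.242 × 0.189 = 0.61.

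Simulated at this d without confounding (4,000 runs), Mann–Whitney has about 88% power and a linear model about 90%. The rank test as such costs little.

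**4. What does missing adjustment cost?** Simulation with no true effect of desaturation, 42 against 84 patients and 4,000 runs per setting. One baseline covariate differs between groups by a given number of SDs and correlates r with FEV1 change. The spurious standardised difference is imbalance × r. Both inputs are assumed. Rejection rates of the unadjusted Mann–Whitney test at p < 0.05:

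| Imbalance (SD) | r = 0.2 | r = 0.3 | r = 0.5 |
|---|---|---|---|
| 0.3 | 6% | 8% | 12% |
| 0.5 | 8% | 12% | 25% |
| 0.8 | 13% | 23% | 52% |
| 1.0 | 17% | 32% | 72% |

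A linear model of the change score adjusted for the same covariate rejects in 4.6% to 6.0% of runs throughout.

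*Hand check of one cell.* At 0.5 SD and r = 0.3 the spurious d is 0.15. Divided by its standard error, 0.15 / 0.189 = 0.79. The normal approximation gives P(Z > 1.96 − 0.79) + P(Z < −1.96 − 0.79) ≈ 0.122 + 0.003 = 0.125, in line with the simulated 12%.

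**5. What the plan already removes.** Working with change takes out differences in baseline level. LLN scaling takes out the age and sex differences carried by the reference values. Neither removes factors that act on the slope, such as baseline severity.

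**The case against.** - **Mann–Whitney is not tied to the primary endpoint by name.** This stands. It is a general rule, and a reader might infer that the plan commits the primary endpoint to it. The text does not go that far; the ANOVA in the sample-size section is the only method linked to the primary power. But no other listed test fits the comparison, and the two sections still disagree.
- **A journal article may leave covariates to a fuller plan.** This stands as far as silence goes. It does not cover two sections that name different analyses.
- **An unadjusted contrast answers part of the aim.** This stands too. Whether desaturators decline faster, as a plain prognostic question, needs no adjustment. Reading desaturation as a driver, or as adding to baseline severity, does, and the Background and Discussion lean that way.
- **The false-positive rates rest on assumed inputs.** They do, and the low end of the range is close to 5%.

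Two stronger readings are tempting but unsupported. One is that a percent-change endpoint mechanically inflates decline in patients with lower baseline FEV1. That holds only if change is taken relative to the patient's own baseline. The Discussion and Abbreviations express FEV1 as a percent of LLN, and for a percentage-point change on that scale the effect disappears. The other is that the repeated-measures ANOVA would lose a specific number of patients through missed visits; the document gives no missed-visit rate.

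**Conclusion.** The concern holds in this form: the 90% power belongs to a four-visit ANOVA that the analysis section does not list, and the only listed test that fits the primary comparison is unadjusted and, in completers, uses two of four visits. The harm comes from missing adjustment and unused data rather than from the rank test's efficiency (about 88% against 90% power for a single change score).

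The size depends on imbalance and correlation, which the article does not give. The false-positive rate is about 12% at 0.5 SD and r = 0.3, and 6% to 72% over the range examined, against about 5% with adjustment. These figures assume 42 and 84 evaluable patients, a two-sided test, and a covariate that is measured and modelled correctly. Adjustment would not remove confounding by factors that are not recorded.

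None of this shows that a positive result would be spurious, or that 148 patients are too few.

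**What to change.** State one primary analysis in the Statistical analysis section and use it in the Sample size discussion:

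- A linear mixed model of FEV1 (percent of LLN) at 0, 12, 24 and 36 months, with group, time and group-by-time.
- A short prespecified set of baseline covariates already collected, each also interacted with time. GOLD stage and GOLD group are known from eligibility. Smoking status should be added if it is recorded; the article does not mention it.
- The adjusted slope difference with its 95% CI, reported beside the unadjusted one so that the plain prognostic contrast stays visible.
- Power restated for this model, with the assumed SD and within-patient correlation.

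No new visits or measurements are needed for the GOLD covariates, and the abstract says recruitment is still under way, so this can be fixed before results are known. The cost is a few degrees of freedom and modest modelling work. With about 42 evaluable desaturators, the covariate list should stay short.
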